### **7.19.2 Post-Treatment Long-Term Follow-up Research Testing**

At time points specified in the schedule of procedures, up to 15 mL of peripheral blood will be drawn and sent to CSL and, if relevant, will be tested for persistence of CAR T cells, clonality, and replication competent lentivirus (RCL) through year 1. During years 2 through 15, samples will be drawn and sent annually only for those subjects with evidence of persistent engraftment of the CAR T cells, or who test positive for RCL. If a patient receives a different lentivirus gene therapy product following treatment on BrainChild-03, they will be expected to have RCL testing for that product and will no longer have specimens collected on BrainChild-03 specifically for RCL.

**Persistence:** PCR for the transgene vector sequence and/or flow cytometric analysis may be done on mononuclear cells to determine the persistence of CAR T cells. Persistence assay testing will be discontinued if patient has had a negative test post their final infusion.

**Clonality:** Patients who at any time point in long term follow up have a >5% increase of cells positive for transgene expression will have a repeat test in 1 month. If the % of cells positive for transgene expression continues to increase, additional testing for clonality will be performed. Clonality may be measured by either examining integration sites or TCR diversity among vector positive cells. If there is evidence of clonality, repeat testing will be performed no later than 3 months.

**Replication Competent Lentivirus (RCL):** Evidence for RCL will be done using VSVg qPCR pre-infusion and at each post-infusion time point during the first year (3, 6 and 12 months). If all post-treatment assays are negative during the first year, then sample collection will be discontinued. For those subjects with positive RCL testing at any time during the 1st year, further time points will be determined by sponsor after review with FDA.

### **7.19.3 Autopsy**

If the research participant dies while on study, then an autopsy will be requested.

## **8 REMOVAL FROM PROTOCOL THERAPY & OFF STUDY CRITERIA**

### **8.1 Removal from Protocol Therapy**

A subject may be discontinued from protocol therapy at any time. Subjects will be removed from protocol therapy for the following reasons:

- Subject/family or the investigator feels that it is not in the subject's best interest to continue
- Subject/family is non-compliant with protocol therapy and/or clinic appointments
- Subject receives medical intervention prohibited under this protocol or which will interfere with the ability to assess toxicity or response following CAR T cell infusion
- Subject experiences a DLT following CAR T cell infusion
- Subject does not meet criteria to receive the next CAR T cell infusion as defined in Section 5.5.2
- Subject is pregnant
- Subject meets criteria for removal from study (Section 8.2)

All subjects who discontinue protocol therapy should come in for an End of Therapy/Early Discontinuation Visit per Appendix 2 – Schedule of Procedures and should be encouraged to complete all remaining scheduled visits and procedures.

### **8.2 Off-Study Criteria and Study Termination**

All subjects are free to withdraw from participation at any time, for any reason, specified or unspecified, without prejudice.

Reasonable attempts will be made by the investigator to provide a reason for subject withdrawals. The reason for the subject's withdrawal from the study will be recorded in the subject's source documents.

Subjects will be removed from the study for the following reasons:

- Subject, or subject's parents/legal guardian, withdraw consent for further participation
- Subject never received CAR T cell product
- Enrolled onto a long-term follow-up protocol for gene therapy
- 15-year anniversary of final CAR T cell infusion
- Death
- Lost to follow-up

The study may be terminated at any time by the Sponsor, the SCH Institutional Review Board (IRB), or the FDA.

## 9 STATISTICAL CONSIDERATIONS

### 9.1 Accrual and Study Duration

Up to 90 patients will be enrolled into BrainChild-03 at Seattle Children's Hospital. Anticipated duration of enrollment accrual is 6 years. Anticipated duration of the active treatment portion of the study is up to 7 months, and anticipated duration of the long-term follow-up period is 15 years.

### 9.2 Primary Objectives

The primary objectives are:

- To assess the feasibility of CNS locoregional adoptive therapy with autologous CD4+ and CD8+ T cells lentivirally transduced to express a B7-H3-specific CAR, EGFRt and a methotrexate resistant human dihydrofolate reductase mutein, delivered by an indwelling catheter into the tumor cavity or ventricular system in children and young adults with DIPG, DMG, or recurrent/refractory CNS tumors.
- To assess the safety of CNS locoregional adoptive therapy with autologous CD4+ and CD8+ T cells lentivirally transduced to express a B7-H3-specific CAR, EGFRt and a methotrexate resistant human dihydrofolate reductase mutein, delivered by an indwelling catheter into the tumor cavity or ventricular system in children and young adults with DIPG, DMG, or recurrent/refractory CNS tumors.
- To establish the tolerability of a fractionated CNS-delivered B7-H3 CAR T cell infusion schedule employing intra-subject dose escalation in children and young adults with DIPG, DMG, or recurrent/refractory CNS tumors.
- To define the maximally tolerated dose (MTD) and Recommended Phase 2 Dose Regimen (RP2DR) of CNS-delivered fractionated B7-H3 CAR T cell infusions.

Feasibility will be described across all subjects and within each therapy Arm and assessed as ability to achieve criteria noted above versus inability to meet each criterion.

Feasibility data will include:

- Number and percent of subjects with sufficient therapeutic product generated to receive two courses at the intended DL per assigned DR after two attempts using a single apheresis product for starting material
- Number of subjects who meet criteria for initial CAR T cell infusion per Section 5.5.1 Requirements for initial CAR T cell infusion
- Number of subjects who meet criteria for at least two courses of CAR T cell infusions per Section 5.5.2 Requirements for subsequent CAR T cell infusion and dose modification

Safety and tolerability data will include:

- History and physical exam (PE) occurring on study and occurring after the CAR T cell infusion
- Laboratory/radiographic evaluations taking place on study and occurring after CAR T cell infusions
- Adverse events

Within each Arm, the toxicities observed with each DR will be summarized in terms of type (organ affected or laboratory determination, such as ANC), severity (by NCI CTCAE v5), CRS grading, neurologic grading, and nadir or maximum values for the laboratory measures, date of onset, and attribution. Tables will be created to summarize these toxicities by Arm and DR with both number of subjects and number of incidences. The evaluation taking place within 2 days prior to initial CAR T cell infusion will serve as the baseline measurement.

### **9.3 Secondary and Exploratory Objectives**

The secondary objectives are:

- To assess B7-H3 CAR T cell distribution within the cerebrospinal fluid (CSF) and the extent to which B7-H3 CAR T cells egress into the peripheral circulation.
- To assess disease response to B7-H3 CAR T cell locoregional therapy in children and young adults with DIPG, DMG, or recurrent/refractory CNS tumors.

Data for evaluation of secondary objectives will include:

- CAR T cell egress will be assessed by analysis of peripheral blood and CSF.
- Tumor response will be assessed using disease response criteria (Section 10.1).
- The duration of overall response will be measured from the initial complete response (CR) or partial response (PR) (whichever is first recorded) until the first date treatment failure is clinically or objectively documented.
- Survival endpoints: progression-free survival (PFS), overall survival (OS), and non-relapse mortality (NRM)

The exploratory objectives are:

- To evaluate for presence of B7-H3 CAR T cells in tumor tissue and/or normal tissue if a tissue biopsy, tumor biopsy, or resection is clinically indicated post-treatment.
- To evaluate B7-H3 expression in tumor tissue and/or normal tissue if a tissue biopsy, tumor biopsy, or resection is available.
- To analyze blood, CSF, and tumor tissue for biomarkers of anti-tumor B7-H3 CAR T cell expression, safety, and activity.

Data for evaluation of exploratory objectives will include:

- B7-H3 status of primary versus recurrent/refractory tumor will be determined by B7-H3 immunohistochemistry (IHC) performed on sequential tumor samples available for each patient.

#### **9.4 Statistical Analysis**

Descriptive statistics, such as mean, standard deviation, and range for continuous variables, and percent and number for categorical variables, will be summarized for baseline information (eg, the extent of prior therapy), and demographic information for each Arm singly and combined. This analysis includes the following variables: race, sex, age, height and weight, stage of disease, tumor characteristics at diagnosis, and others if applicable.

#### **9.5 Safety and Tolerability**

Subjects receiving any CAR T cell product will be eligible for safety and tolerability analyses. If a subject is removed from study prior to receiving the initial CAR T cell infusion, they will be replaced. For the purpose of assessing overall safety and tolerability, subjects will be evaluated for toxicities for up to 28 days following final CAR T cell infusion. For the purposes of escalation of DR and defining Maximal Tolerated Dose Regimen (MTDR), subjects in the existing cohort will be evaluated for toxicities from the time of initial CAR T cell infusion through 7 days following the final CAR T cell infusion received during Course 2, or until they commence with alternate therapies for their CNS tumor, whichever comes first. Subjects who are taken off study prior to Day 28 of Course 2 and have experienced a DLT will count towards that DR's evaluable accrual and will not be replaced. For all Arms, if a subject is removed from study prior to Day 28 of Course 2 for reasons other than toxicity (e.g., progressive disease requiring immediate alternative therapy) and has not received at least one dose of the maximally intended dose level per the assigned DR, they will be replaced before cohort advancement is permitted. Subjects who die before Day 28 of Course 2, and before receiving alternative therapy, and whose death is due to CAR T cell related toxicity will meet the definition of DLT and will not be replaced. Subjects who die before Day 28 of Course 2 due to reasons other than CAR T cell related toxicity and have not experienced a DLT will be replaced before cohort advancement is permitted.

#### **9.6 Survival Definitions**

OS: Time from CAR T cell infusion to death from any cause. If a subject is alive at the last evaluation time period, survival time is censored at the time of last follow-up.

PFS: Time from CAR T cell infusion to the first observation of disease progression or death from any cause, whichever occurs first. If the subject has not progressed, relapsed or died, progression-free survival is censored at the time of last follow-up.

NRM: Time to death event where cause of death is not attributable to underlying disease. Relapse and progression, including death attributable to underlying disease, are treated as competing risks for NRM and censored at time of last follow-up for those who do not relapse, progress or die.

Analysis of survival endpoints will include all subjects who receive at least one B7-H3 CAR T cell infusion and will be summarized for all subjects and by cohort. PFS and OS will be assessed using Kaplan Meier (K-M) estimates, and NRM will be assessed using cumulative incidence estimates. The following will be presented for both PFS and OS:

- K-M curves
- The median K-M expected survival time and 95% confidence interval
- Six-month and 12-month K-M survival estimates with 95% confidence intervals

The following will be presented for NRM:

- Cumulative Incidence curves
- Median expected survival and 95% confidence interval
- Six-month and 12-month and 95% confidence intervals

## **9.7 Evaluability for Dose Escalation**

A subject will be considered DR escalation-evaluable if they are evaluable for toxicity (see Section 9.5 Safety and Tolerability), and were counted as part of a 3-subject dose escalation cohort according to the rules described in Section 9.9.1 Arms and DLT observation periods during Course 1 and 2.

## **9.8 Evaluability for Disease Response**

A subject will be considered evaluable for disease response if: (1) the subject meets the eligibility criteria to receive the CAR T cell infusion; (2) the subject receives the CAR T cell infusion; and (3) the subject is under follow-up for a sufficient period to evaluate the disease and meets criteria for having evaluable disease (Section 10.1 Disease Response Criteria). For the purposes of the study, response will be assessed in comparison to the Treatment Response Evaluation performed within 28 days prior to the initial T cell infusion. Response will be characterized following Course 2 and, if available, at the completion of additional Courses. A subject who dies as a result of toxicity after receiving T cell product but prior to initial response assessment following Course 2 will be considered a non-responder.

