#### **3.2 Eligibility**

##### **3.2.1 Inclusion criteria**

1. Subjects must be age  $\geq 1$  and  $\leq 26$  years (except for the first 3 subjects, who will be enrolled in Arm A or Arm B and must be age  $\geq 15$  and  $\leq 26$  years) (this requirement has been met as of 8/27/2020).
2. Subject disease classified as one of the following:
  - a. DIPG at any timepoint following completion of standard radiotherapy
  - b. DMG at any timepoint following completion of standard radiotherapy
  - c. Evidence of refractory or recurrent CNS disease for which there is no standard therapy, defined by either of the following (further categorization by disease type is listed in Appendix 5 –Refractory and Recurrent Disease Categorization):
    - i. Recurrent disease (e.g., new site(s) of measurable or evaluable disease by radiographic imaging or histologic confirmation following completion of standard of care first-line therapy for which curative salvage therapy is not available or amenable), OR
    - ii. Refractory disease (e.g., measurable or evaluable disease that persists following completion of standard of care first-line therapy for which curative salvage therapy is not available or amenable)
3. Able to tolerate apheresis or already has an apheresis product available for use in manufacturing
4. CNS reservoir catheter, such as an Ommaya or Rickham catheter, present in the proper location for CNS-directed therapy delivered as specified for BrainChild-03
5. Life expectancy  $\geq 8$  weeks
6. Lansky or Karnofsky score  $\geq 60$ . Subjects who are unable to walk because of paralysis, but who are up in a wheelchair, will be considered ambulatory for purposes of assessing performance status

7. If subject does not have a previously obtained apheresis product that is acceptable and available for manufacturing of CAR T cells, subject must discontinue all anticancer agents and radiotherapy and, in the opinion of the investigator, have fully recovered from significant acute toxic effects of the following:
  - a. *Cytotoxic chemotherapy/biologic therapy*: All cytotoxic chemotherapy/biologic therapy must be discontinued  $\geq 7$  days prior to enrollment.
  - b. *Antibody Therapy*: The last dose of anti-tumor antibody therapy (including checkpoint inhibitor) must be at least 3 half-lives or 30 days, whichever is shorter, from the time of enrollment. Bevacizumab will be considered biologic therapy.

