### **7.18.1 Disease response assessment during active treatment**

Disease Response will be assessed within 1 week following the last CAR T cell infusion on even courses (e.g., 2, 4...) but may be delayed up to 4 weeks due to clinical or scheduling issues. This evaluation must be performed prior to receiving Week 1 CAR T cell infusion on the subsequent odd course (e.g., 3, 5...).

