| Concomitant Medications                                                                                                          |           | X         | Continuous through Day+28 P  |                |          |                |          |                |        |          |                |          |                |          |                |        |                     |          |          |                                    |                                     |   |                                           |                  |

\* Treatment Plan delays may be allowed, see Section 5.1.6.

- a Evaluations must be performed prior to study enrollment, but have no specific procedure window
- b Evaluations must be performed within 7 days prior to study enrollment. Results of standard-of-care tests or examinations performed prior to obtaining informed consent may be used
- c Evaluations must be performed within 28 days prior to study enrollment. Results of standard-of-care tests or examinations performed prior to obtaining informed consent may be used
- d Evaluations must be performed within 3 months prior to study enrollment. Results of standard-of-care tests or examinations performed prior to obtaining informed consent may be used
- e Evaluations must be performed within 2 days prior to any apheresis (See [Section 5.3](#) for repeat apheresis criteria)
- f Evaluations must be performed within 2 days prior to CAR T cell infusion unless the infusion is omitted in which case evaluations are optional (See [Section 5.1.6](#))
- g Infusions must be performed  $\geq 7$  days after the previous infusion
- h Evaluations must be performed 2 to 5 days after CAR T cell infusion unless the infusion omitted in which case evaluations are optional (See [Section 5.1.6](#)). Post-infusion evaluations, except Correlative Sciences evaluations, may be used for infusion or Week 4 evaluations if performed within the required window. Distinct Correlative Sciences evaluations must be completed at every timepoint
- i Evaluations may be performed at any point during Week 4 +/- 3 days. Evaluations are optional for odd courses beyond Course 2

- j Required prior to Course 1 Week 1 if bridging therapy received AND >28 days from prior scans, or if clinically indicated

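### The response denominator in 9.8 can leave out early disease deaths and subjects without a post-infusion scan, because only toxic deaths are scored as non-response

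*Protocol*

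**What the plan says.** Protocol 9.8 sets three conditions for response evaluability: the subject meets the infusion criteria, receives the infusion, and both has evaluable disease and satisfies this: "the subject is under follow-up for a sufficient period to evaluate the disease". The length of that period is not given.

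The section fixes the timepoint: "Response will be characterized following Course 2 and, if available, at the completion of additional Courses". Section 7.18.1 adds the timing, "Disease Response will be assessed within 1 week following the last CAR T cell infusion on even courses", and says that this "may be delayed up to 4 weeks due to clinical or scheduling issues".

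One early-loss group is given an outcome. "A subject who dies as a result of toxicity after receiving T cell product but prior to initial response assessment following Course 2" is counted as a non-responder. Section 9.8 names no other early loss.

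On the baseline, 9.8 says that "response will be assessed in comparison to the Treatment Response Evaluation performed within 28 days prior to the initial T cell infusion". The schedule in Appendix 2 places the screening MRI within 28 days before enrollment (footnote c). Footnote j, in both Table 1a and Table 1b, repeats it under narrower terms: "Required prior to Course 1 Week 1 if bridging therapy received AND >28 days from prior scans, or if clinically indicated".

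**The concern.** The sentence on toxic deaths is needed only if an early death would otherwise fail the follow-up condition. Because it stops at toxicity, a subject who dies of disease before any assessment has no rule that keeps them in the denominator, although that is a plain treatment failure.

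Such losses are foreseeable. "Life expectancy" at entry need only be at least 8 weeks, judged before apheresis and manufacture. Section 9.5 itself provides for deaths from non-toxic causes before Day 28 of Course 2, though only for cohort replacement. OS and PFS (9.6) include every infused subject; response does not, and no reason is given.

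Disease response is a secondary objective. Under 9.9.4 a lower dose regimen with satisfactory response may also be chosen as the RP2DR, at investigator discretion and with DSMB approval.

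**Working it through.** The protocol states no response rate, target or early-loss rate, so there is no planned figure to reproduce. The check has three parts.

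**1. Where each early course ends up**

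| Before the Course 2 assessment | What the protocol provides | In the denominator? |
|---|---|---|
| Death from toxicity | 9.8: non-responder | Yes |
| Progression on the early-discontinuation MRI | 7.18.2, 8.1 and schedule footnote l (MRI within 28 days of last infusion); PD in Table 10-1 | Yes |
| Switch to other therapy, with that scan | Same route; scored from the scan | Yes |
| Death from disease, no assessment | No rule | Can be left out |
| Alive, no post-infusion scan | No rule; footnote k ties disease evaluation to clinical indication | Can be left out |
| Symptomatic deterioration without imaging progression | Named in 10.1.6; no row in Table 10-1 | Unassigned |

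**2. Effect of omission**

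Let n subjects be infused, r respond, and k non-responders be omitted, with d = k/n.

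- All infused: r/n. Evaluable only: r/(n − k). Ratio: n/(n − k) = 1/(1 − d).
- d = 5%: 1/0.95 = 1.05. d = 10%: 1/0.90 = 1.11. d = 20%: 1/0.80 = 1.25. d = 30%: 1/0.70 = 1.43.
- An assumed true rate of 20% would be reported as 21.1%, 22.2%, 25.0% and 28.6%.
- Expansion cohort of 12 (section 9.10) with an assumed 2 responders: 2/12 = 16.7% (exact 95% CI 2.1% to 48.4%). Dropping three gives 2/9 = 22.2% (2.8% to 60.0%).

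*How large d might be.* The last Course 2 infusion falls in week 7 if nothing is delayed, so the assessment falls at about week 8, or about week 11 with the permitted delay. Section 5.1.6 also allows each infusion in Courses 1 and 2 to slip by up to 3 weeks. Assume exponential survival from first infusion, so the proportion dead by week t is 1 − 0.5^(t/M), with M the median in weeks (months × 52/12). The medians are assumptions:

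| Assumed median | Dead by week 8 | Dead by week 11 |
|---|---|---|
| 4 months | 27% | 36% |
| 6 months | 19% | 25% |
| 9 months | 13% | 18% |
| 12 months | 10% | 14% |

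These are deaths from any cause. Some of these subjects would have had an early-discontinuation scan or died of toxicity, and so would already count. The figures show that losses before the assessment are plausible; they do not estimate d.

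**3. The baseline scan**

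A subject who received no bridging therapy has a screening MRI up to 28 days before enrollment. Apheresis and manufacture follow, and 9.9.1 staggers first infusions between subjects. Unless a repeat is clinically indicated, footnote j does not call for one. The subject can follow the schedule exactly and still lack the baseline that 9.8 specifies. Because 10.1.4 measures partial response against the initial baseline, growth between scan and infusion goes unseen. It hides later shrinkage or is scored as progression, so the error runs mainly downward.

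**The case against.** The strongest reply is that 9.8 never says disease deaths are excluded. That is an inference from an undefined follow-up condition and a sentence limited to toxicity. The point stands as a description of the text, but the text also offers no rule that would count these subjects.

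A reader might go further and infer that everyone who progresses clinically or switches therapy before the Course 2 scan is dropped. The documents do not support that. Subjects who stop are asked to attend an end-of-therapy visit, 7.18.2 calls that assessment required, its MRI is due within 28 days of the last infusion and may come from a local provider, and progression on it is PD. Section 10.1.6 also asks that objective progression be documented after stopping. The follow-up condition does not literally require reaching the Course 2 scan either; an earlier scan can satisfy it. What remains is the group with no scan or with unassigned symptomatic deterioration.

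It is also fair that response is descriptive, with no test or threshold, that PFS and OS in all infused subjects keep early failures visible, and that the RP2DR route is discretionary and needs at least six DLT-evaluable subjects. In a cohort of 12 the illustrated shift lies well inside either confidence interval. These points limit the consequence; they do not supply the missing rule.

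**Conclusion.** The concern holds for early deaths not due to toxicity, subjects without a post-infusion scan, and symptomatic deterioration before the first assessment. As written, 9.8 lets them leave the denominator, and each omitted non-responder raises the reported rate. The factor 1/(1 − d) assumes that none of those omitted responded. The range 1.05 to 1.43 and the move from 16.7% to 22.2% are illustrations under assumed losses, since the protocol gives no early-loss rate. Neither the actual size of the bias nor a difference between arms or dose regimens can be derived from it.

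The baseline conflict between 9.8 and footnote j is real for non-bridged subjects but is a separate matter. A reader might take it as a second source of inflation; an older baseline would mainly bias response downward. Nor can it be counted on to offset the denominator problem, because the two need not affect the same subjects.

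**What to change.** In 9.8:

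- Make the main response denominator all infused subjects with evaluable disease at baseline.
- Score death from any cause, clinical progression or symptomatic deterioration, or start of other anticancer therapy before the first post-baseline assessment as non-response.
- Drop the follow-up condition from the main denominator. Report the current evaluable set as a sensitivity analysis, with its required follow-up period defined.

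This is a wording change that brings response into line with the all-infused set used for PFS and OS. The cost is a slightly less favourable reported rate.

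Separately, reconcile the baseline window in 9.8 with footnote j of Tables 1a and 1b, so that a subject who follows the schedule has the baseline that the analysis uses. Which passage should change is for the sponsor to decide.

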### **5.4 Bridging Therapy**

During the period between apheresis and CAR T cell infusion, subjects may return to the care of their primary physician. Additional therapy aimed at controlling disease burden to allow the subject to meet criteria for CAR T cell infusion may be given. Refer to Section 5.5.1 Requirements for initial CAR T cell infusion and Table 5-2 for Pre-T Cell Therapy Wash-Out Requirements.

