### **5.5 CAR T Cell Product Infusion**

#### **5.5.1 Requirements for initial CAR T cell infusion**

The following criteria must be met prior to administration of initial CAR T cell product:

- First 3 subjects (this requirement has been met as of 8/27/2020):

- Age  $\geq 15$  and  $\leq 26$  years
  - Only treated on Arm A or Arm B
- Subjects subsequent to the first 3 treated:
  - Age  $\geq 1$  and  $\leq 26$  years
  - May be enrolled on any Arm (Note: See Section 9.9.1 Arms and DLT observation periods: Subjects may be enrolled on Arm C once 3 subjects have been treated on Arm A and/or Arm B, and at least 1 subject on Arm A or B completes Course 2 without experiencing a DLT. This requirement has been met as of 04/29/20.)
- Subject has a CNS reservoir catheter in place
- Subject is  $\geq 5$  days from CNS surgery, including catheter placement
- Subject has confirmed evidence of persistent, evaluable disease
- Subject is not breastfeeding
- Female subjects of childbearing potential only: subject has a negative pregnancy test within 2 days prior to initial CAR T cell infusion
- Regarding bridging therapy:
  - If the subject has achieved defined partial or complete remission with bridging therapy, the Study Chair or designee will recommend to the subject's treating oncologist that the bridging therapy be continued. The subject may be re-evaluated and would be eligible to receive CAR T cell treatment upon meeting requirements for CAR T cell infusion.
  - The following treatments must be discontinued for the specified duration (washout period) prior to infusion of the CAR T cell product, and subject must have recovered from acute therapy associated toxicities.

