**Table 5-2 Pre-T Cell Therapy Washout Requirements**

| Treatment                                                                                                                                                     | Wash-out Period
(prior to CAR T cell product infusion) |
|----------------------------------------------------------------------------------------------------------------------------------------------------------------------|------------------------------------------------------------------|
| Radiation therapy                                                                                                                                                    | ≥ 6 weeks                                                        |
| Bevacizumab                                                                                                                                                          | ≥ 28 days                                                        |
| Cytotoxic chemotherapy                                                                                                                                               | ≥ 21 days                                                        |
| Biologic agents                                                                                                                                                      | ≥ 7 days                                                         |
| Antibody therapy
(eg, murine, chimeric or
humanized monoclonal
antibodies)
T cell growth factors
(eg, IL-2, IL-7 or IL-15)
Interferons
Vaccines | ≥ 3 half-life or 30 days
(whichever is shorter)               |
| Cellular therapy                                                                                                                                                     | ≥ 30 days since last infusion                                    |
| Any investigational agent                                                                                                                                            | ≥ 3 half-life or 30 days
(whichever is shorter)               |

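### Section 9.8 does not require the response baseline scan to follow tumour resection or bridging, so shrinkage before the first infusion can be scored as response

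*Protocol*

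**What the plan says.** Section 9.8 sets the reference for response: "response will be assessed in comparison to the Treatment Response Evaluation performed within 28 days prior to the initial T cell infusion". The only condition on that scan is its distance from the infusion.

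Tumour-reducing treatment is permitted inside the same 28 days. Section 5.5.1 requires at least 5 "days from CNS surgery, including catheter placement". Section 5.4, on the time between apheresis and infusion, says: "Additional therapy aimed at controlling disease burden to allow the subject to meet criteria for CAR T cell infusion may be given". Table 5-2 sets the wash-outs, with 7 days for biologic agents and 21 days for cytotoxic chemotherapy.

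The repeat MRI before Course 1 is governed by footnote j, which has the same rule in Appendix 2, Table 1a (Arms A and B) and Table 1b (Arm C): "Required prior to Course 1 Week 1 if bridging therapy received AND >28 days from prior scans, or if clinically indicated".

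Section 5.5.1 has two related provisions. The subject must still have confirmed, evaluable disease. On bridging it says "If the subject has achieved defined partial or complete remission with bridging therapy, the Study Chair or designee will recommend" to the treating oncologist that bridging go on.

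Section 10.1.4 measures PR as a decrease of at least 50% from the initial baseline. It measures PD as an increase of at least 25% over the smallest sum seen since treatment began.

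**The concern.** A baseline for response to a product should describe the tumour as it stood when the product was first given. Here the reference scan may describe a tumour that was later cut back or shrunk by other treatment, before any CAR T cell was infused. PR is judged against that scan, so the earlier reduction counts towards response. PD is judged against the smallest sum recorded since treatment began. If the reduced tumour was never measured before infusion, regrowth from it can go unseen, and PFS is then affected too.

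Response is a secondary objective. Under Section 9.9.4 a satisfactory response at a lower dose regimen can also support choosing that regimen as RP2DR.

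**Working it through.** The protocol states no response rate or sample size that depends on the baseline scan, so there is no figure of its own to reproduce.

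**1. Exposed days.** Take a baseline scan on day -28. The interval in which treatment can fall after the scan and before infusion is 28 minus the minimum gap, and never below 0.

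| Treatment | Minimum gap (source) | Exposed days |
|---|---|---|
| CNS surgery | 5 days (5.5.1) | 28 - 5 = 23 |
| Biologic agents | 7 days (Table 5-2) | 28 - 7 = 21 |
| Cytotoxic chemotherapy | 21 days (Table 5-2) | 28 - 21 = 7 |
| Bevacizumab | 28 days (Table 5-2) | 0 |
| Cellular therapy | 30 days (Table 5-2) | 0 |
| Radiation | 6 weeks (Table 5-2) | 0 |

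These are calendar maxima, not frequencies.

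**2. Does footnote j close the interval?** Its mandatory part needs both bridging and scans more than 28 days old. That age limit equals the window in 9.8, so the mandatory part does not apply to any scan that qualifies as a baseline. It does not mention surgery. Only the discretionary clinical-indication clause remains.

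**3. Effect on PR.** Let x be the shrinkage between baseline scan and infusion, and y the further shrinkage needed for PR. Then (1 - x)(1 - y) = 0.50, so y = 1 - 0.50/(1 - x). The values of x are assumptions, because the protocol gives none.

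| x before infusion | y needed after infusion |
|---|---|
| 0% | 50% |
| 25% | 33.3% |
| 40% | 16.7% |
| 49% | 2.0% |
| 50% or more | 0% |

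After 60% removal, the remnant could grow by 25% and still read as PR, since 0.40 x 1.25 = 0.50.

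**4. Illustration with assumed sizes.** A lesion is 30 x 30 mm before resection (900), 14 x 14 mm after it (196), and 20 x 20 mm after Course 2 (400).

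- Against the pre-operative scan: 400/900 - 1 = -55.6%, which is PR.
- Against the post-operative residual: 400/196 - 1 = +104%, which is beyond the 25% limit for PD.

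**5. Non-measurable residual.** Section 10.1.2 lets disease be evaluable without being measurable. A subject whose target lesion was wholly resected can therefore still meet the 5.5.1 requirement. If non-target disease persists, Table 10-1 combines target CR with non-target SD into an overall PR.

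**6. Weight of one subject.** In an expansion cohort of 12, one such response moves the rate by 1/12 = 8.3 percentage points. Among six subjects, the DLT-evaluable minimum in 9.9.4, it moves it by 1/6 = 16.7 points if all six are also evaluable for response.

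**The case against.** **Safeguards.** Section 5.5.1 steers a subject in remission on bridging towards more bridging, and it requires disease still to be present. Footnote j allows a scan when clinically indicated, which could cover a resection. This stands as mitigation. But continuing bridging is only a recommendation and does not reach surgery or shrinkage short of PR. Persistent disease can be smaller disease. The clinical-indication clause is discretionary. None of these resets the baseline.

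**Route into Arm A.** Because Arm A infuses into a tumour cavity, a reader might infer that resection shortly before infusion is the usual path and that Arm A is mainly affected. The protocol does not support this. Inclusion criterion 4 (Section 3.2.1) requires the catheter to be in place already. Apheresis, unless a product exists, and manufacture then come before infusion. No manufacturing time is given, so a pre-operative scan inside 28 days is possible but not shown to be common.

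**Direction.** Bias can run the other way: growth between scan and infusion counts against the product. This is true, and it is another reason to use the latest scan.

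**Left to the SAP.** Choosing among several pre-infusion scans is often an SAP matter, and the SAP is not at hand. Section 9.8 nevertheless sets the baseline rule itself, and its wording admits a scan that precedes the reduction.

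**Conclusion.** The point holds as a cheap improvement. Following 9.8 and footnote j as written, tumour removed or shrunk before any CAR T cell can be scored as response, and later growth can be masked. The exposed interval is at most 23 days for surgery, 21 for biologics and 7 for cytotoxics. The size of the error depends on shrinkage the protocol does not state, and the number of subjects affected is unknown.

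Two stronger readings should be resisted. The text does not say such tumour is scored as response in general. That needs a scan that predates the treatment and no later scan taking its place. Nor does response decide the RP2DR. The MTDR rests on the DLT rate, and response can only support a lower regimen, by investigator discretion, with DSMB approval and at least six DLT-evaluable subjects.

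**What to change.** In Section 9.8, define baseline as the last available MRI before the first infusion and, where tumour resection or bridging took place in between, the last one after it. State that catheter-only surgery does not reset the baseline, so a valid scan is not lost to an operation that left the tumour unchanged.

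Where no scan follows the resection or bridging, flag the subject and report the response rate with and without flagged subjects. Do not force a non-response for a missing scan.

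For subjects with a qualifying scan, the exposed interval falls from up to 23, 21 or 7 days to 0, and PR always needs a 50% decrease from the tumour as last measured after that treatment.

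The cost is a few sentences in 9.8 and one extra line in the response table. The downside is that a few responses will be flagged as not clearly attributable to the product. No surgery interval or wash-out changes, and no extra MRI is mandated, so footnote j can stay as it is.
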